To meet our secondary objective of investigating health service utilisation in multimorbid patients, we will use a retrospective cohort design. We will create a cohort of patients beginning on January 1, 2012 and following these patients over four years until December 31, 2015. The exposed group will be all patients who have multimorbidity as of January 1, 2012, and the unexposed group will be patients who do not have multimorbidity. We will look at the relationship between the exposure of multimorbidity and the outcome of health service utilisation, which will be assessed based on number of GP consultation, number of prescription medications, and number hospital admissions over the four-year follow-up period. This study design will help us account for the effect of differential mortality that may potentially occur between the exposed and unexposed groups. Mortality will be a secondary outcome in our four-year follow-up. Any patients who have transferred out of their practice during the follow-up period will be censored.

1. **Sample Size**

*Please provide an estimate of sample size, and, where possible, a formal power calculation. An estimate of the expected number of patients available in the CPRD database should normally be included.*

For our primary objective of describing the prevalence of multimorbidity, we have calculated a sample size estimate of 425,400 patients.

This sample size calculation was obtained using the following formula for calculating sample size in cross-sectional studies of prevalence^21^.

$$n=\frac{Z^{2}P\left( 1-P \right)}{d^{2}}$$

In this formula, *n* is the sample size and Z is the test statistic corresponding to a 95% confidence level. P is the expected prevalence of multimorbidity. We set P to be 23.2%, which was the prevalence of multimorbidity obtained by the Barnett *et al.* study on a similar population in Scotland^4^. *d* is the precision of the estimate, corresponding to the effect size. We set size *d* to be 0.13%, which was based on the 95% confidence intervals of the prevalence of multimorbidity from the Barnett, *et al* paper^4^*.*

Using the LSOA “Linked Source Data”, we observed that there are currently 95.2% English patients who have patient level IMD data.  We therefore increased our sample size from 405,000 to 425,400 to account patients who will have to be dropped due to missing IMD data.

1. **Data Linkage Required (if applicable)**

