*Please provide a synopsis of the purpose(s) for which the each of the linkages requested in section 18 of the application form is required.*

The proposed linkage of GOLD data to the patient-level Index of Multiple Deprivation (IMD) dataset will enable us to obtain an estimate of socioeconomic status, which we consider a key predictor of multimorbidity^4,5,22^. The proposed linkage to the Integrated Hospital Episode Statistics (HES) datasets will allow us to obtain much more complete ethnicity data^23^, which we believe to be an important predictor of multimorbidity that has not been adequately addressed in the current literature^24^. It will also allow us to obtain information about the number of hospital admissions, which is one of our outcomes for measuring health service utilisation.

1. **Study Population**

*Define the source and study population, in terms of persons, place, time period, and listing the criteria which will be used to select the study population from the CPRD, i.e any inclusion or exclusion criteria. Please make clear any restrictions imposed by the use of linked datasets.*

A random sample without replacement of approximately 425,400 patients taken from all adults 18 years or older who were currently registered with a GP on or before December 31, 2015.

1. **Selection of comparison group(s) or controls**

*Describe the criteria for eligibility and the procedure for control selection.*

For the retrospective cohort component of our study, cases are all patients in the dataset who have multimorbidity, defined as having two or more of the morbidities listed in Appendix A. The comparison control group will consist of patients who either have zero or one current morbidities in their medical record.

1. **Exposures, Outcomes and Covariates**

*For exposures and outcomes operational definitions (or procedures for developing them) must be provided, supported by preliminary code lists placed in an Annex. A comprehensive list of covariates should also be provided for any study which is not purely descriptive.*

*Exposures and Outcomes for Primary Research Objective:*

Since this is a descriptive study, we do not have a specific exposure for our primary objective. However, we will consider several covariates in our analysis including age, sex, ethnicity, socioeconomic status (using IMD deciles), smoking status, and region.

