The outcome of our descriptive analysis is the prevalence of multimorbidity, and we will define multimorbidity using a list of 36 comorbidities (Appendix 1). See Section D for the rationale for choosing these specific morbidities.

In addition to describing the prevalence of multimorbidity, as part of our descriptive analysis we are interested in the pairing and clustering of different comorbidities. To assess the frequency of the most commonly paired comorbidities, our outcome will be pairs of any two separate morbidities from the code list of 36 comorbidities. Additionally, to evaluate our final descriptive outcome relating to the prevalence of physical-mental health comorbidities, mental health comorbidities will be defined as Depression and Anxiety, Alcohol Problems, Dementia, Learning Disability, and Schizophrenia or Bipolar Disorder. All other morbidities will be defined as physical (See Appendix 1).

*Exposures and Outcomes for Secondary Research Objective:*

Our secondary research objective is to investigate the association between multimorbidity and health service utilisation. The exposure for this four-year retrospective cohort study is multimorbidity, which has been defined above.

We will consider three patient-level health service utilisation outcomes:

- the number of GP practice consultations (in-person or by phone)
- the number of prescriptions a patient has been issued
- the number of hospital admissions.

We will consider mortality as a secondary outcome of the retrospective cohort component of our study.

1. **Data/ Statistical Analysis**

*This section should cover both the analytic methods and also the analyses which are to be performed to meet all the specific aims listed earlier. It is important to ensure that this section is clear and specific about any comparisons which will be made*

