**Appendix 1: List of the 36 disease conditions to be included in multimorbidity count**

| Code | Condition | *Criteria* |
| --- | --- | --- |
|  |  |  |
| HYP | Hypertension | *Read Code ever recorded* |
| DEP | Depression and Anxiety | *Read code recorded in last 12 months OR >=4 anti-depressant prescriptions (excluding low dose tricyclics) in last 12 months OR >=4 anxiolytic/hypnotic prescriptions in the last 12 months* |
| PNC | Painful condition | *>=4 POM analgesics in last 12 months OR >= 4 specified anti-epileptics in the absence of an epilepsy Read code in last 12 months* |
| AST | Asthma (currently treated) | *Read code ever recorded AND any asthma prescription in the last 12 months.* |
| CHD | Coronary heart disease | *Read Code ever recorded* |
| DIB | Diabetes | *Read Code ever recorded* |
| THY | Thyroid disorders | *Read Code ever recorded* |
| RHE | Rheumatoid arthritis, other inflammatory polyarthropathies & systematic connective tissue disorders | *Read Code ever recorded* |
| HEL | Hearing loss | *Read Code ever recorded* |
| COP | COPD | *Read Code ever recorded* |
| IBS | Irritable bowel syndrome | *Read code ever recorded OR ≥ 4 prescription only medicine antispasmodic prescription* |
| CAN | New diagnosis of cancer in last five years | *Read code first recorded in last 5 years* |
| ALC | Alcohol problems | *Read Code ever recorded* |
| OPS | Other psychoactive substance misuse | *Read Code ever recorded* |
| CON | Constipation (Treated) | *≥4 laxative prescriptions in last year* |
| STR | Stroke & transient ischaemic attack | *Read Code ever recorded* |
| CKD | Chronic kidney disease | *Best of the last 2 GFR readings <60* |
| DIV | Diverticular disease of intestine | *Read code ever recorded* |
| ATR | Atrial fibrillation | *Read code ever recorded* |
| PVD | Peripheral vascular disease | *Read code ever recorded* |
| HEF | Heart failure | *Read code ever recorded* |
| PRO | Prostate disorders | *Read code ever recorded* |
| EPI | Epilepsy (currently treated) | *Read code ever recorded AND antiepileptic prescription in last 12 months* |
| DEM | Dementia | *Read code ever recorded* |
| SCZ | Schizophrenia (and related non-organic psychosis) or bipolar disorder | *Read code ever recorded/recorded in last 12 months OR Lithium prescribed in last 168 days* |
| PSO | Psoriasis or eczema | *Read code ever recorded AND ≥ 4 related prescriptions in last 12 months (excluding simple emollients)* |

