| IBD | Inflammatory bowel disease | *Read code ever recorded* |
| MIG | Migraine | *≥ 4 prescription-only anti-migraine prescriptions in last year* |
| BLI | Blindness and low vision | *Read code ever recorded* |
| SIN | Chronic sinusitis | *Read code ever recorded* |
| LEA | Learning disability | *Read code ever recorded* |
| ANO | Anorexia or bulimia | *Read code ever recorded* |
| BRO | Bronchiectasis | *Read code ever recorded* |
| PRK | Parkinson’s disease | *Read code ever recorded* |
| MSC | Multiple sclerosis | *Read code ever recorded* |
| CLD | Chronic Liver Disease and Viral Hepatitis | *Read code ever recorded* |

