**Amendment 2**

The following amendment is proposed, as of 24/09/2018:

Investigators

The research team would like to add statisticians [name], [name], [name] and [name] to the project.

Objectives

We wish to update Objective 5:

1. To determine patterns of multimorbidity disease combinations associated with health service utilisation outcomes, treatment burden, mortality, index of multiple deprivation and age in order to identify clusters of patients that are in some respect “similar.”

Data Linkage Required (if applicable)

To assess the relationship between multimorbidity clusters and mortality, we additionally wish to link ONS mortality data.

Data/Statistical Analysis

We propose to use profile regression (see below) instead of latent class analysis to cluster patients based on their health conditions. Formally, profile regression is a latent class analysis, with the addition that clusters are sought which are related to the outcome. As described above, we will generate clusters associated with health service usage, treatment burden (number of current prescription medications), mortality, index of multiple deprivation and age. This will ensure the clusters found are relevant to those outcomes, and so will be most useful. Rather than random effects for practices, we will study the impact of practice-level variation by adding it as a fixed effect co-variate into our model. We will perform cross-validation to ensure the robustness of our results.

**Reference for profile regression:** https://arxiv.org/abs/1303.2836

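### Nine of the 36 conditions that make up the exposure are defined partly or wholly by prescriptions, so the association of multimorbidity with prescription count is partly definitional wherever prescribing persists

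*Protocol*

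**What the plan says.** Under Exposures, Outcomes and Covariates, the secondary objective is set out as an association: "The exposure for this four-year retrospective cohort study is multimorbidity, which has been defined above". The comparison-group section classes patients as multimorbid, "defined as having two or more of the morbidities listed in Appendix A" (the list itself is headed Appendix 1), against those with none or one. Study Design fixes the date: "The exposed group will be all patients who have multimorbidity as of January 1, 2012". Follow-up then runs to 31 December 2015.

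The utilisation outcomes are consultations, hospital admissions and "the number of prescriptions a patient has been issued". For aim 4, the Data/Statistical Analysis section plans separate regressions of each outcome on the number of morbidities, crude and adjusted.

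Appendix 1 gives the criteria. Constipation is "≥4 laxative prescriptions in last year". Painful condition is ">=4 POM analgesics in last 12 months", or a similar rule on specified anti-epileptics. Migraine is four or more "prescription-only anti-migraine prescriptions in last year". None of these three asks for a diagnosis code. Six further conditions use prescriptions alongside or as an alternative to a code.

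**The concern.** If a condition is recognised because a drug was issued repeatedly in 2011, and the outcome is how many prescriptions are issued from 2012 on, continued prescribing of that drug raises both sides. A patient whose only listed conditions are painful condition and constipation is classed as exposed on at least 4 + 4 = 8 prescriptions and no diagnosis code. The prescribing ratio would then mix two things: that people with more disease are prescribed more, and that people selected for being prescribed to continue to be prescribed to. Consultations and admissions do not share this direct overlap, because no Appendix 1 criterion counts them. At stake is the interpretation of one of the three utilisation outcomes. The primary prevalence objective is not affected.

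**Working it through.** **Step 1: tally of the Appendix 1 criteria.**

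| Role of prescriptions | Conditions | Number |
|---|---|---|
| Sole criterion | Painful condition (PNC), constipation (CON), migraine (MIG) | 3 |
| Sufficient without a code | Depression and anxiety (DEP), irritable bowel syndrome (IBS), schizophrenia or bipolar disorder (SCZ) | 3 |
| Required in addition to a code | Asthma (AST), epilepsy (EPI), psoriasis or eczema (PSO) | 3 |
| Not used | All others | 27 |

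So 9/36 = 25% use prescriptions, 6/36 = 17% can be met by prescriptions with no diagnosis code, and 3/36 = 8% have no other route. Six use a rule of four or more (PNC, CON, MIG, DEP, IBS, PSO). SCZ needs only lithium within 168 days, and AST and EPI need any relevant prescription in 12 months.

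**Step 2: timing.** With exposure fixed at 1 January 2012, the 12-month look-backs fall in 2011, and the outcome is counted from 2012 to 2015. Nothing is counted on both sides. The link can arise only through persistence of prescribing from one window to the next.

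**Step 3: what the plan has against it.** The confounding section adjusts for age, sex, deprivation, ethnicity, smoking and region, with random effects for practice. Practice effects can absorb differences in habit between practices. They cannot absorb one patient's continuing prescriptions relative to another patient in the same practice. The four listed limitations include severity as a confounder of medication number, but not shared definitions. The only sensitivity analysis named for a utilisation outcome concerns consultation type.

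**Step 4: size under a null.** The protocol gives no prescribing rates, so there is no figure of its own to reproduce and every rate below is an assumption. In both set-ups the code-defined conditions have no effect on prescribing. The measure is

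ratio = mean follow-up prescriptions in the multimorbid ÷ mean in the rest,

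and its true value under this null is 1.

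*Class-specific persistence.* N = 425,400; the three prescription-only conditions each arise from four or more issues in their own drug class in the baseline year; about 11% of patients have at least one of them; multimorbidity about 19%; a mean of 6 other prescriptions a year, unrelated to anything else. The share of patients whose class-specific prescribing rate carries into follow-up is varied:

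| Share persisting | Ratio, full count | Ratio, prescription-only conditions dropped |
|---|---|---|
| 0% | 1.00 | 1.00 |
| 25% | 1.04 | 1.00 |
| 50% | 1.09 | 1.01 |
| 75% | 1.13 | 1.00 |
| 100% | 1.17 | 0.99 |

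Other runs of this kind, with different assumed rates, reached 1.19.

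*One shared prescribing tendency.* N = 400,000; a mean of 12 prescriptions a year; a single gamma frailty per patient drives every drug class; six prescription-defined and ten code-defined conditions. As the frailty shape rises from 0.5 (strong variation between patients) to 2 (weaker), the ratio falls from 3.23 through 2.26 to 1.78. With a count built on codes only it is 1.00, 0.98 and 1.00. This set-up makes 6/16 = 38% of conditions prescription-defined, against 17% in Appendix 1 that can be met without a code, so it leans high. Shared-frailty runs with multimorbidity prevalence of 21-25%, near the 23.2% in the sample-size section, gave 1.03 to 2.2.

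**The case against.** The strongest reply is that the aim is descriptive. Repeated analgesic or laxative issue is the protocol's chosen marker of a current, treated condition, and its continuation is part of the burden to be described. The windows are separate, 27 of 36 conditions use no prescription criterion, and an extra sensitivity analysis might sit in an analysis plan that is not to hand.

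Much of this stands. The overlap is partial, it vanishes if prescribing does not persist, and for a plain table of prescribing by number of conditions it does little harm. But the protocol also names an exposure and an outcome, plans crude and adjusted regressions, and has a confounding section. An adjusted prescribing ratio will be read as saying something about disease. The problem lies in the definitions that the protocol itself fixes. Appendix 2 already drops treated dyspepsia because acid-suppressing drugs are increasingly given to prevent side effects of other medicines, which accepts that a drug-based marker can track prescribing rather than disease.

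A reader might infer more than the protocol supports:

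- That follow-up prescriptions are mostly the same repeat items as in 2011. The protocol gives no figure on this.
- That the prescribing ratio will be set against the consultation and admission ratios. The three relationships are to be examined separately, and no such comparison is planned.
- That the treatment-burden outcome in Amendment 2 repeats the fault. Those clusters are deliberately sought in relation to the outcomes, and Amendment 3 moves outcome-guided clustering to a methodological paper.
- That a ratio near 3 is the expected bias. It needs a strong shared frailty, for which the protocol offers no evidence.

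**Conclusion.** The concern holds in a limited form. The exposure contains nine prescription-based definitions, three of them with no other route, and one of the three utilisation outcomes is a count of prescriptions. Where prescribing persists, part of that association is definitional, and nothing in the plan removes or acknowledges it. The direction under persistence is upward. The amount is not known: about 1.0 to 1.2 under class-specific persistence and up to about 3 under a strong shared tendency, all on assumed rates. It is a point worth correcting for one secondary outcome, and it does not undermine the study.

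**What to change.** For the prescription-count outcome in aim 4, prespecify one sensitivity analysis and present it beside the main result. It would do one or both of the following:

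- (a) Drop PNC, CON and MIG from the morbidity count and remove the prescription-only route for DEP, IBS and SCZ. Leave AST, EPI and PSO as defined: they have no separate code route, and dropping the prescription requirement would turn currently treated disease into disease ever coded.
- (b) Keep the full count, but remove the defining drug classes of all nine conditions from the outcome.

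The two do different work. (b) removes class-specific persistence but not a tendency shared across classes, because that would still drive the drugs left in the outcome. (a) acts on both, apart from the small part that remains through AST, EPI and PSO. Doing both is therefore more informative than either alone.

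Interpret the prescribing association in the light of the result, and add the overlap to the limitations. The headline definition of multimorbidity need not change.

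Cost: one extra analysis with codes that already exist. (a) uses a narrower count than the headline definition, and (b) leaves out some real prescribing burden, which is why neither should replace the main result.

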To meet our third aim of examining mental morbidities and the linkage of physical and mental comorbidities, we will report the percentage of individuals with both a physical and mental comorbidity. We will use a logistic regression, controlling for sociodemographic characteristics, to quantify the association between mental and physical morbidities, with the binary outcome being the presence of a mental health comorbidity. We will report odds ratios and covariate adjusted odds ratios of having any mental health disorder based on the number of physical morbidities an individual has. We will also report the odds ratios by sociodemographic characteristics. Additionally, we will use a chi-squared test to assess differences between the prevalence of any multimorbidity and the prevalence of having a physical-mental health comorbidity between our sociodemographic covariates described in Section K.

To meet our fourth aim of describing health service utilisation, we will use the total number of consultations as the denominator to evaluate the proportion of consultations devoted to patients with different levels of multimorbidity. We will also use the mean and standard deviation of the number of consultations and prescriptions to describe consultation and prescribing rates in relation to the number of morbidities. We will calculate the total number of consultations, prescriptions, and hospitalisations a patient has during our four-year study period, and will explore the patterns of the data to determine the most appropriate form of regression to look at the separate relationships between the number of morbidities and the number of consultations, prescriptions, and hospitalisations. In this analysis, we will adjust for patients who died during the four-year follow-up as well as for patients who have been censored due as a result of transferring out of the practice. We will use a Cox proportional hazards model to describe the differences in mortality rate between exposed multimorbidity patients and non-multimorbid patients. All regression analyses will consist of a crude analysis in addition to an adjusted one incorporating the covariates described in Section K.

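### The hospital outcome counts maternity admissions as if they were illness admissions; report admissions with and without them, above all for the 18–44 stratum

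*Protocol*

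**What the plan says.** Under Exposures, Outcomes and Covariates, the third utilisation outcome of the secondary objective is "the number of hospital admissions", with no further definition. Data Linkage Required names the source, saying of the HES linkage: "It will also allow us to obtain information about the number of hospital admissions, which is one of our outcomes for measuring health service utilisation". The fourth-aim text in Data/Statistical Analysis fixes the window: "We will calculate the total number of consultations, prescriptions, and hospitalisations a patient has during our four-year study period".

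The Study Population section describes a sample "taken from all adults 18 years or older who were currently registered with a GP on or before December 31, 2015", with no restriction by sex or pregnancy. Exposed patients have two or more of the 36 listed conditions. For the others, "The comparison control group will consist of patients who either have zero or one current morbidities in their medical record". Pregnancy is not on the Appendix 1 list, and no section mentions maternity.

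On analysis: "All regression analyses will consist of a crude analysis in addition to an adjusted one incorporating the covariates described in Section K". Age and sex are among those covariates. The Technical Summary counts hospitalisations among the primary outcomes of the cohort part. The Limitations section plans a sensitivity analysis with narrower and broader definitions for GP consultation type; there is none for admissions.

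Aim 5 links disease patterns to health service use, and Amendment 2 keeps that link. Amendment 3 runs the latent class analysis within age strata, the youngest being 18–44, and describes the approach taken so far as learning clusters first and comparing them with outcomes afterwards.

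**The concern.** Read as written, a delivery in a healthy woman and an emergency admission for heart failure each add one to the same count. Maternity admissions occur only in women of childbearing age. If they depend on multimorbidity less than illness admissions do, they add events to both exposure groups in a proportion that dilutes the ratio. This is not confounding, so no covariate removes it.

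The stake for the headline adjusted ratio is small, because women of childbearing age supply only part of all admissions. It is larger where they supply much of the count, which is the 18–44 stratum. There, a cluster made up largely of women could look like a heavier hospital user because of births rather than its pattern of disease. In the adjusted model the coefficient for female sex would also absorb maternity use.

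**Working it through.** **The plan's own figure.** The protocol has no figure on admissions. Its only sizing concerns prevalence, and it reproduces: 1.96² × 0.232 × 0.768 / 0.0013² = 405,018 (stated 405,000), and 405,000 / 0.952 = 425,420 (stated 425,400). It has no bearing on this point.

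**Direction.** Within a stratum let *a* be the illness admission rate in the 0–1 group, *R* the true multimorbidity ratio for illness admissions, *m* the maternity admission rate in the 0–1 group, and *k* the multimorbid to non-multimorbid ratio of maternity rates. Then

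observed ratio = (R·a + k·m) / (a + m), and R − observed = m(R − k) / (a + m).

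The observed ratio lies below R whenever k < R. If k = R, nothing changes within the stratum.

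**Assumptions, set A (none from the documents except the age bands, borrowed from Amendment 3).**
- Ages 18–44, 45–64, 65–84 and 85+; shares of adults 45, 33, 19 and 3%; sexes equal.
- Multimorbidity 8, 22, 50 and 70%, giving 0.036 + 0.0726 + 0.095 + 0.021 = 22.5% overall, close to the protocol's planning value of 23.2%.
- Four-year non-birth admissions in the 0–1 group: 0.25, 0.35, 0.8 and 1.3.
- R = 2 or 3 at every age; m = 0.1 to 0.3 per woman aged 18–44 over four years; k = 0.7 to 1.0.

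**Women aged 18–44.**
- R = 2: (0.50 + 0.10)/0.35 = 1.71, down to (0.50 + 0.21)/0.55 = 1.29.
- R = 3: (0.75 + 0.10)/0.35 = 2.43, down to (0.75 + 0.21)/0.55 = 1.75.

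**Whole 18–44 stratum, sexes pooled (m halved).**
- R = 2: (0.50 + 0.05)/0.30 = 1.83, down to (0.50 + 0.105)/0.40 = 1.51.
- R = 3: (0.75 + 0.05)/0.30 = 2.67, down to (0.75 + 0.105)/0.40 = 2.14.

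**Crude ratio, R = 2.** Without births, the 0–1 group has 0.28129/0.7754 = 0.363 admissions per patient and the multimorbid group 0.27542/0.2246 = 1.226, a ratio of 3.38. With m = 0.1 and k = 1, the numerators gain 0.0207 and 0.0018, and the ratio is (0.27722/0.2246)/(0.30199/0.7754) = 3.17. With m = 0.3 and k = 0.7 they gain 0.0621 and 0.00378, and the ratio is 2.81.

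**Adjusted ratio.** A Poisson model was fitted to the expected counts with age band, sex and multimorbidity. Adding an age-by-sex interaction left the multimorbidity ratio unchanged to three decimals.

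**Assumptions, set B.** Seven age bands; 0.07 to 0.36 non-maternity admissions per year by age in the 0–1 group; R = 1.8; multimorbidity about 24%; maternity admissions 0.06 to 0.14 per woman-year at ages 18–27, 1.2 times that at 28–37 and a quarter of it at 38–47.

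| Ratio | Set A, R = 2 | Set A, R = 3 | Set B, R = 1.8 |
|---|---|---|---|
| Crude | 3.38 → 3.17–2.81 | 5.07 → 4.74–4.19 | 3.11 → 2.78–2.45 |
| Adjusted, overall | 2.00 → 1.97–1.90 | 3.00 → 2.94–2.80 | 1.80 → 1.77–1.73 |
| Young women (A: 18–44; B: 18–37) | 2.00 → 1.71–1.29 | 3.00 → 2.43–1.75 | 1.83 → 1.45–1.29 |

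The crude ratio falls by about 6 to 17% in set A and 11 to 21% in set B. The adjusted ratio falls by about 1 to 7% and 2 to 4%. With no true sex difference, the adjusted female:male ratio rises from 1.00 to 1.06–1.24 in set A and 1.14–1.32 in set B.

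**The case against.** The strongest reply is that nothing is misstated. The study calls itself primarily descriptive, its objective is health service use, and total admissions is a legitimate measure of that, useful for planning resources. Which HES episodes count could be set out in an analysis plan not shown here. This stands in large part. It is why the all-admission count should be kept, and why the point is an improvement only. It does not dispose of the point: the protocol form asks for operational definitions of outcomes in this section, and the authors did specify consultations, with a sensitivity analysis, while leaving admissions bare.

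Second, the adjusted ratio hardly moves, and the crude one is a poor guide anyway. In set B it is 3.11 before any births are counted, against a true 1.8, so age confounding inflates it by 73% (3.11/1.8 = 1.73) and counting births moves it towards the true value. This also stands; the crude fall on its own would not justify a change.

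Third, every rate is assumed. If antenatal admissions are commoner in multimorbid women, k rises, the attenuation shrinks, and excluding these admissions would discard real exposure-related use. That argues for showing both versions rather than replacing one by the other. So does Amendment 4, which records that HES has already been used to look at hospitalisation, so that replacing the outcome now would be post hoc.

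A reader might also infer that planned comparisons of admissions by sex and by age are distorted. The documents do not support this: the sex and age tests under the first aim concern multimorbidity and the mean number of morbidities, and no standalone comparison of admissions by sex or age is planned. What is affected is the sex coefficient in the adjusted model and any results within the youngest age stratum.

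**Conclusion.** The point holds as a modest improvement. As written, the outcome mixes maternity with illness admissions, and the planned adjustment cannot separate them. If k < R, which is plausible but not shown in the documents, the association is attenuated slightly in the overall adjusted estimate, more in the crude estimate, and most in young women.

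It would go too far to say that the main adjusted result is seriously biased; the calculations do not show that. The case for change rests on the 18–44 stratum. That the clusters there are compared on hospital use is a reading of aim 5, Amendment 2 and Amendment 3 together, since Amendment 3 does not itself name hospital use as the outcome for that stratum.

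The calculations contrast two or more conditions with none or one, as Study Design does. The fourth-aim regression uses the number of morbidities; the same algebra applies to each level against the reference, but the sizes would differ.

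**What to change.** In Exposures, Outcomes and Covariates, state that maternity admissions will be identified from HES fields (admission method, episode type or obstetric codes) and counted separately. In Data/Statistical Analysis, report the admission regressions, and the comparison of clusters on hospital use in the 18–44 stratum, both for non-maternity admissions and for all admissions. This mirrors the sensitivity analysis that the Limitations section already plans for consultation type.

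The cost is one classification rule on data already linked, one extra version of the outcome, and one extra table. The all-admission count remains as the description of total hospital activity, so nothing now planned is lost.
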